
## 3 Discussion

This study aims to explore whether LVO-AIS patients in the Western Sichuan Plateau can benefit from endovascular treatment. Given the challenges many countries face with an aging population and the increasing burden of cerebrovascular diseases, research on stroke in plain areas has been extensive. In contrast, stroke-related research in high-altitude regions is relatively scarce. This study may offer some hope for clinical treatment of AIS patients in the Western Sichuan Plateau and similar regions, helping to alleviate stroke-related issues. However, as this study only includes LVO-AIS patient data from the Western Sichuan Plateau, its findings may provide treatment recommendations specifically for clinical practice and decision-making in high-altitude areas of China. The generalizability of these results to other high-altitude regions worldwide remains to be validated. Furthermore, as a follow-up study, it is inevitable to encounter loss of follow-up bias. In addition to conducting telephone interviews and follow-up visits upon returning to the hospital, we also attempted to conduct multidimensional follow-up through WeChat survey mini-programs to reduce bias. In summary, potential biases will be minimized through standardized protocols and adjustments for baseline parameters, ensuring the robustness and validity of the study findings.

The FOML model addresses common challenges in multimodal data fusion, particularly in complex applications such as medical image analysis, genomics research, and multi-task learning. In these domains, integrating data from diverse sources (e.g., images, gene expression, and clinical data) often requires managing heterogeneity, including differences in features, distributions, and noise. Traditional multimodal learning approaches often overlook modal differences or fail to effectively balance the contributions of each modality, limiting model performance. To tackle this issue, the FOML model employs a combination of progressive fusion, orthogonal sequential fusion, and dynamic balancing mechanisms. This approach allows for finer-grained adjustment of the fusion process, maximizing the contribution of each modality to the final prediction.

The key advantage of the FOML model lies in its ability to handle imbalanced information across modalities. Progressive fusion effectively retains fine-grained information from earlier layers by gradually integrating features, while avoiding the information loss and feature conflicts common in traditional early fusion methods. Orthogonal sequential fusion applies weighted fusion to each modality in sequence, reducing inter-modal interference and preserving the independence and diversity of each modality. Balanced multimodal learning dynamically adjusts learning strategies for each modality, addressing the challenge of uneven contributions and enhancing model performance in complex multi-task learning scenarios. Together, these techniques optimize the model's robustness in the face of data imbalance, noise interference, and high-dimensional feature spaces, making it particularly suitable for high-complexity tasks such as medical imaging and genomics data analysis.

In terms of experimental design, we will validate the FOML model on multiple multimodal medical datasets, encompassing various data types such as image data, gene expression data, and clinical data. To assess the performance of the FOML model compared to traditional fusion methods (e.g., progressive fusion, orthogonal sequential fusion, and balanced multimodal learning) in handling different tasks and data types, we will employ standard statistical analysis methods, including paired *t*-tests, analysis of variance, and Kruskal-Wallis tests, to ensure the statistical significance of performance differences between models. We will pay particular attention to the model's performance in the presence of noise and modality imbalance. We expect the FOML model to demonstrate higher accuracy and robustness under these challenges compared to traditional methods, further validating its superiority and potential applications in multimodal learning tasks.

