**Conclusion:**

This study aims to evaluate the efficacy of endovascular treatment compared with standard medical therapy in patients with LVO-AIS in the Western Sichuan Plateau and to develop an artificial intelligence–based prognostic model to refine treatment strategies for this and other high-altitude regions.

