In the Western Sichuan Plateau, due to its unique geographical and climatic conditions, the incidence and mortality rates of stroke may be higher than in lowland areas, potentially linked to factors such as the hypoxic environment, cold climate, and lifestyle habits of the residents. Our previous meta-analysis (10) showed that the stroke prevalence is higher in high-altitude regions, with variations observed across different sampling types and geographical locations. Age, female gender, hypertension, and obesity are identified as potential risk factors in this population. However, it remains unclear whether patients with AIS in high-altitude areas benefit from EVT.

In recent years, the rapid development of machine learning is expected to enhance the predictive accuracy of the prognosis for certain treatment methods. The key advantage of the fused optimized multimodal learning model lies in its ability to handle imbalanced information across modalities. Progressive fusion effectively retains fine-grained information from earlier layers by gradually integrating features, while avoiding the information loss and feature conflicts that often arise in traditional early fusion methods (11). Orthogonal sequential fusion sequentially weights each modality's data, reducing inter-modal interference and ensuring the independence and diversity of each modality (12). Balanced multimodal learning dynamically adjusts the learning strategies for each modality, addressing the challenge of uneven contributions and improving the model's performance in complex multi-task learning scenarios (13). Together, these methods optimize the model's robustness in the presence of data imbalance, noise interference, and high-dimensional feature spaces, making it particularly suitable for high-complexity tasks such as medical imaging and genomics data analysis.

This study aims to prospectively collect data from LVO-AIS patients in the Western Sichuan Plateau to explore the efficacy of EVT in this population, providing evidence for endovascular interventions for AIS patients in the region. Furthermore, after validating the effectiveness of EVT for LVO-AIS in the Western Sichuan Plateau, an artificial intelligence-based prognostic prediction model will be developed using relevant data, significantly facilitating the treatment of AIS patients in this region.

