### 2.5 Machine learning model

This study proposes a novel multimodal learning model—fused optimized multimodal learning (FOML)—designed to enhance the effectiveness of multimodal data fusion through progressive fusion, orthogonal weighting, and dynamic balancing mechanisms. First, the progressive fusion method retains the advantages of deep fusion while avoiding the feature loss issues associated with traditional early fusion approaches. By gradually integrating information across different layers, this method ensures that shallow-level features guide deeper fusion processes. This approach is expected to perform exceptionally well in future medical image analysis, particularly in scenarios combining imaging and clinical data, where diagnostic accuracy and model generalization capabilities are likely to see significant improvement (11). Secondly, the orthogonal sequential fusion (OSF) strategy sequentially weights and fuses data from each modality, using an adaptive mechanism to reduce inter-modal interference and enhance the unique information extraction capability of each modality. When dealing with data from modalities with significant dimensional differences, such as CT images, MRI scans, and genomic data, the OSF strategy can effectively improve the model's accuracy (12). Finally, the balanced multimodal learning framework addresses the issue of uneven contributions across modalities by dynamically adjusting the learning rate for each modality. In particular, in multi-task learning scenarios, it optimizes the objective function for each modality, enhancing overall task performance and preventing any single modality from exerting excessive influence (13). The method ensures the balanced integration of multimodal data, including images, genomic, and clinical information, in medical image classification tasks, thereby improving diagnostic efficiency and robustness. The FOML model combines three approaches: through the progressive layered fusion, orthogonal weighted fusion, and dynamic balancing mechanisms, not only enhances model accuracy but also strengthens its adaptability to noise and complex data, achieving multi-level integration. Additionally, considering that FOML operates at the task-wise in meta-learning, we implement a three-stage task division: meta-training, meta-validation, and meta-testing. Tasks are grouped and partitioned by domain/subject/scene/institution/time period to ensure mutual exclusivity among the three stages. To mitigate domain transfer overfitting risk, we apply Leave-One-Domain-Out (LODO) cross-validation, sequentially designating each domain as meta-test while using the remaining domains for meta-training and meta-validation, reporting cross-domain averages and variances. All inner-loop updates are constrained by a fixed number of steps and incorporate weight decay and gradient clipping; in cases of class imbalance, task-wise resampling or cost-sensitive loss functions are employed. Final reported metrics and interval estimates (via bootstrap or Bayesian hierarchical models) pertain solely to meta-test tasks, with explicit exclusion of hyperparameter tuning or reuse based on meta-validation tasks.

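### Every comparator named for the AI model is one of its own components and none is a clinical-variable model, so the benchmark as written is an ablation and does not address added prognostic value

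*Protocol article*

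**What the plan says.** **Purpose of the model.** The Conclusion of the Abstract states the aim "to develop an artificial intelligence–based prognostic model to refine treatment strategies for this and other high-altitude regions". The Introduction says that, once EVT has been shown to be effective in this population, "an artificial intelligence-based prognostic prediction model will be developed using relevant data".

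**What the model is.** Section 2.5 says: "The FOML model combines three approaches: through the progressive layered fusion, orthogonal weighted fusion, and dynamic balancing mechanisms". It explains the third part as follows: "the balanced multimodal learning framework addresses the issue of uneven contributions across modalities by dynamically adjusting the learning rate for each modality". The Discussion gives the same composition: "the FOML model employs a combination of progressive fusion, orthogonal sequential fusion, and dynamic balancing mechanisms".

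**How it will be judged.** The last paragraph of the Discussion says "we will validate the FOML model on multiple multimodal medical datasets" and plans to assess performance "compared to traditional fusion methods (e.g., progressive fusion, orthogonal sequential fusion, and balanced multimodal learning", with significance tests on the differences between models. It expects FOML to come out ahead and treats that as support for its superiority.

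**How the article uses the word traditional elsewhere.** The Introduction, section 2.5 and the Discussion attach it to early fusion. In the Discussion, progressive fusion is credited with its benefits "while avoiding the information loss and feature conflicts common in traditional early fusion methods".

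**The concern.** A benchmark should be something that the new method could replace. Here the named benchmarks are what the new method is made of. Comparing a combined model with each of its parts is an ablation study: it is useful for showing that the combination earns its complexity, but it does not measure the model against existing practice.

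For a prognostic model meant to inform treatment, the question is whether it predicts a patient's outcome better than variables every stroke service already records. If FOML beats its three components, that question stays open, yet the planned conclusion is one of superiority over traditional methods. A reader of the final report could take this as evidence that multimodal AI adds to clinical prediction in these patients when no stated comparison had tested it.

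The stake is not trivial. Section 2.2 says that each group was doubled in size to serve the machine learning work, so half of the planned cohort rests on this aim.

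**Working it through.** There is no performance figure to reproduce. The check sets the statements side by side.

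**Step 1. Components against named comparators.**

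| Component of FOML (section 2.5; Discussion) | Named comparator (Discussion, last paragraph) |
|---|---|
| Progressive (layered) fusion | Progressive fusion |
| Orthogonal sequential (weighted) fusion | Orthogonal sequential fusion |
| Dynamic balancing, which section 2.5 describes as the working principle of balanced multimodal learning | Balanced multimodal learning |

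Result: 3 of 3 named comparators are components. None is early fusion, a single-modality model or a clinical-variable model.

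**Step 2. The label.** The article presents the three techniques as the remedy for the weaknesses of traditional early fusion and of traditional approaches that handle modalities unevenly. The last paragraph of the Discussion then calls the same three techniques traditional. Both uses cannot hold. On the article's own usage, the traditional fusion method is early fusion.

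**Step 3. How far *e.g.* reaches.** The list is introduced by *e.g.*, so other members of the class may be intended. The class is traditional fusion methods. Early fusion fits it. A logistic regression on baseline clinical variables fuses no modalities and does not fit it. The open list therefore leaves room for early fusion, but not for a clinical-variable benchmark.

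**Step 4. What would be needed, and whether the data exist.** Section 2.4 lists the propensity score covariates: age, sex, NIHSS at baseline, time from onset, comorbid disease and imaging findings. These are collected and can carry a simple prediction model. Section 2.5 already provides testing on held-out domains and interval estimates by bootstrap or Bayesian hierarchical models. All the ingredients of a clinical benchmark are present; the comparison itself is not stated.

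**Step 5. How much of the sample rests on this aim.** Inputs from section 2.2: 0.191 versus 0.326, significance level 0.05 (two-sided, section 2.4), power about 90%, 20% dropout, then doubling. The pooled two-proportion formula is

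n = [1.960·√(2·p̄(1−p̄)) + 1.282·√(p₁(1−p₁)+p₂(1−p₂))]² / (p₂−p₁)², with p̄ = (0.191+0.326)/2 = 0.2585.

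This gives 219 per group (power 90.01%). Then 219 × 1.2 = 262.8, rounded up to 263, and 263 × 2 = 526, the stated group size. The doubling accounts for 526 − 263 = 263 per group, or 526 of the 1,052 patients. How the dropout allowance was applied is a separate matter and does not affect this point.

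**The case against.** The strongest reply has four parts.

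- **The list is open.** This stands. A reader might infer that FOML will be compared with nothing but its own parts. The text does not say so, and early fusion may be intended.
- **A condensed article can leave reference models to the full protocol or analysis plan, and the covariates are there.** This stands against the stronger inference that the study could never show added value: nothing in the design prevents fitting a clinical model. It does not dispose of the point. The article chose to state the comparator class, the tests and the expected conclusion, and what it states is mislabelled and does not match the aim.
- **The article claims superiority only in multimodal learning, and for that claim comparison with each published technique alone is legitimate.** As an ablation it is. But the Abstract and Introduction promise a prognostic model for patients, and a methods claim about fusion does not deliver that.
- **The validation wording should not be overread.** This stands. A reader might infer that validation takes place away from this cohort, or that gene expression contradicts the data collection in sections 2.1 to 2.3. Neither is supported. Several datasets do not exclude this one; the Introduction and section 2.2 tie the model to the cohort, and section 2.5 allows domains split by institution. Gene expression is mentioned as a data type of the validation datasets, and the article does not list the baseline variables in full. What remains is a lack of clarity about which datasets are external.

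Nor do the documents give any ground for saying that a simple regression would in fact do as well as FOML. That is unknown, which is why it should be tested.

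**Conclusion.** The point holds in this form: all three named comparators are FOML's own components, they are called traditional against the article's own usage, and the stated class of comparators leaves out any clinical-variable model. As written, the benchmark is an ablation and does not address whether FOML predicts 90-day outcome better than routine baseline variables.

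The size cannot be expressed as a number, since no performance target or estimate is given. In scope, it affects what the second aim can conclude, an aim for which the sample was doubled. It leaves the EVT estimate, the primary outcome and the main analysis untouched.

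Two assumptions underlie this. First, the model's prediction target is the study's primary outcome, mRS 0–2 at 90 days; neither section 2.5 nor the Discussion names the target. Second, no unseen document states a clinical benchmark. If one does, the remaining correction is to the label and to the wording of the superiority claim.

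**What to change.** 1. Describe progressive fusion, orthogonal sequential fusion and balanced multimodal learning as ablations of FOML, and name early fusion as the traditional fusion comparator.
2. Add a pre-specified logistic regression, penalised if preferred, for mRS 0–2 at 90 days, using the baseline covariates already listed in section 2.4 plus treatment received. Fit it on the same training domains as FOML and evaluate it in the same held-out domains of this cohort, with any tuning kept out of the test domains.
3. Report the differences between FOML and this model in discrimination and calibration, with bootstrap intervals taken on the same test patients for both models.
4. Rest any claim of added prognostic value on that comparison alone. Ablation results and results on other datasets may support statements about the fusion method.
5. State which validation datasets are external to the cohort, including any with gene expression data.

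The cost is one simple model on data already collected and a few changed sentences. No study procedure, visit or sample size changes. The real price is that FOML may look less favourable against a plain regression than against its own parts.
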